- pain catastrophizing scale (PCS)^5^
- hospital anxiety and depression scale (HADS)^6^
- sexual function (PISQ-IR)^7^
- Visual analog scale (VAS) score ^8^
  - 1. Anatomical outcomes
- Pelvic floor hypertonicity measured by the MAPLe device
  - 1. Other outcomes
- A cost-effectiveness analysis will be performed in case of a significant improved VAS score and quality of life.
  1. One year follow-up

To evaluate the safety and efficacy of a BTA injection one year after BTA injection.

- 1. Open label extension study

To evaluate the safety of BTA injection 26 weeks after the placebo injection in participants who did not reach the primary endpoint.

1. **Study methods**
   1. Study design

Double-blinded randomized placebo-controlled trial.

- 1. Study population

Patients over 16 years with >6 months of chronic pelvic pain with pelvic floor muscle hypertonicity refractory to first-line pelvic floor physiotherapy, and in whom no anatomical cause was found.

* Definition by the International Continence Society: Chronic pelvic pain is characterized by persistent pain lasting longer than 6 months or recurrent episodes of abdominal/pelvic pain, hypersensitivity or discomfort often associated with elimination changes, and sexual dysfunction often in the absence of organic etiology^9^.

- 1. Inclusion criteria
- Female, >16 years
- Chronic pelvic pain according to the ICS with or without dyspareunia
- Vaginal examination with one finger possible
- Pelvic floor hypertonicity measured by physical examination by registered pelvic floor physiotherapist and MAPLe
- Previous physical therapy with registered physical therapist was unsuccessful
- Good understanding of Dutch language
- Willing to provide informed consent
  1. Exclusion criteria
- (wish for) Pregnancy/lactation during study period
- Previous pelvic floor BTA treatment
- Known hypersensitivity to BTA
- History of neuromuscular or bleeding disorders
  1. Treatment of subjects

The pelvic floor muscles will be injected with either 100 IU BTA or placebo.

- 1. Study procedures

The subjects will undergo the following procedures after signing informed consent:

- Physical examination by a gynecologist and a physical therapist
- MAPLe measurement by a physical therapist
- The patient preference questionnaire will be filled in
- The validated questionnaires will be filled in at baseline, 4, 8, 12 and 26 weeks after injection
- Injection of study medication or placebo in pelvic floor muscles

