- Standardized physical therapy by an experienced registered pelvic floor physical therapist during the study period
- Deblinding of subjects who did not meet the primary endpoint and offer them a second injection with BTA.
- As part of the Open-label Extension Study, subject will fill in validated questionnaires at 4, 8, 12 and 26 weeks after BTA injection.
- One year follow-up questionnaires will be filled in after the primary BTA/placebo injection or one year after the BTA injection in case of the Open-label Extension Study.
  1. Study medication and preparation

The investigational medicinal product (IMP) will either be Botulinum Toxin Type A 100IU or 0.9% NaCl (placebo).

The BTA and placebo will be supplied from site stock, where it is stored according to Good Distribution Practice (GDP ), recommended respectively in Dutch hospital pharmacies and outpatient clinics. The drugs will become investigational medicinal products only when they are made ready for administration.

The independent health professional, not involved in the study or treatment of the patient, will prepare the syringe with the investigational medicinal product under aseptic conditions just before administration. The independent health professional will dissolve 100IU BTA in 6cc 0.9% NaCl in a syringe or only 6cc 0.9% NaCl in a syringe, depending on the treatment arm. This process will always be verified by a second, independent person (controller) to assure that the process is done correctly.

- 1. Randomization procedure and blinding

Participants were randomly allocated to BTA injection or placebo injection in a 1:1 ratio. The 94 sealed opaque envelopes were randomly divided across the inclusion centres and opened on the day of randomization. The gynaecologist, physical therapist and participant were blinded to the treatment arm. Participants who did not meet the primary endpoint (33% reduction VAS score or PGI-I 1 or 2) were deblinded after 26 weeks. Participants who received placebo injection were offered to participate in our open label extension study and receive BTA injection concurrent with pelvic floor physical therapy.

[figure not shown]

Figure 1. flow-chart RCT

[figure not shown]

Figure 2. flow-chart follow-up studies after ending of RCT: one year follow-up and open-label extension study

- 1. Replacement of individual subjects after withdrawal

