1. Is the occurrence of missing data random, or is there a discernible pattern among these individuals?
2. What is the source of the missing data?
3. Is there any correlation with specific variables?
4. Can we identify a pattern in the missing data?

Based on the answers to these questions, the potential options for the pattern of missing data are as followed: Missing completely at random (MCAR), missing not at random (MNAR), and missing at random (MAR).

In case of additional analyses not performed using mixed models, missing data will be examined and if necessary randomly imputated.

Patients who are lost to follow-up will be censored at the last visit on which all assessments were completed.

- 1. Interim Analyses and Data Monitoring

No interim analyses are planned.

1. **Efficacy analyses**
   1. Timing of final statistical analysis

The statistical analyses of the primary outcome and secondary outcomes (measured 26 weeks after treatment) will be performed after a minimum of 26 weeks have elapsed from the inclusion of the final patient in the study and after data cleaning for these outcomes has been completed.

The statistical analysis of the follow-up study will be performed 26 weeks after inclusion of the final patient and data cleaning for these outcomes has been completed.

- 1. Primary and secondary outcome analysis

The null hypothesis entails that there is no significant difference in decrease of chronic pelvic pain scores 26 weeks after treatment between the intervention group receiving BTA injections and the control group receiving placebo injections among women with chronic pelvic pain.

VAS score Analysis:

- Mixed models for repeated measurements will be used. VAS scores will be compared over time between groups
- Primary endpoint: Percentage difference in VAS score between baseline and 26 weeks post-treatment will be calculated for each group.

PGI-I Analysis:

- Mixed models for repeated measurements will be used.
- PGI-I scores will be analyzed to identify differences between groups over time.
- Primary endpoint: the primary outcome of PGI-I scores being 1 or 2 (presented as median and interquartile (IQ) range) will be compared between groups.

Secondary outcome analysis

Questionnaire Scores:

- The total scores of all questionnaires will be analyzed over time using mixed models for repeated measurements.
- Analysis will involve assessing changes over time between groups MAPLe

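### The SAP times the follow-up analysis 26 weeks after the last inclusion, but its own schedule needs at least 52 weeks for the last woman's one-year data and at least 78 weeks if she enters the extension

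*SAP*

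**What the plan says.** Under Efficacy analyses, Timing of final statistical analysis, the SAP gives two rules.

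- **RCT.** The analysis of the primary and secondary outcomes comes "after a minimum of 26 weeks have elapsed from the inclusion of the final patient" and after those outcomes have been cleaned.
- **Follow-up.** "The statistical analysis of the follow-up study will be performed 26 weeks after inclusion of the final patient", again with cleaning of the relevant outcomes completed. Here the 26 weeks is a fixed time and not a lower bound.

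The follow-up schedule is set out elsewhere in the SAP.

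- Endpoints, One year follow-up gives the objective: "To evaluate the safety and efficacy of a BTA injection one year after BTA injection".
- Endpoints, Open label extension study reads: "To evaluate the safety of BTA injection 26 weeks after the placebo injection in participants who did not reach the primary endpoint".
- Study methods, Study procedures fixes the questionnaires: "One year follow-up questionnaires will be filled in after the primary BTA/placebo injection or one year after the BTA injection". The second alternative applies to extension participants. The same section lists extension questionnaires at 4, 8, 12 and 26 weeks after the open-label injection.
- Study methods, Randomization procedure and blinding puts deblinding, and hence the offer of the open-label injection, after week 26. The title of Figure 2 places both follow-up components after the RCT has ended.

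The SAP gives no later time for the follow-up analysis anywhere else.

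**The concern.** The follow-up study is given the same 26 weeks as the RCT, although its data are due much later. On the plain reading, the last woman included is only just reaching the RCT endpoint on the day the follow-up analysis is scheduled. If she goes on to the extension, her open-label injection can be no earlier than that day.

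If the sentence were followed, the one-year safety and efficacy results would come from women included early enough to have completed the year, and later-included women would drop out for administrative reasons alone. The SAP has a rule for women who are lost to follow-up but none for women whose assessment is not yet due. A reader of the follow-up report could not tell from the plan which women should have been in the analysis.

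**Working it through.** **Inputs, all from the SAP**

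- Stated time of the follow-up analysis: 26 weeks after the last inclusion (Timing of final statistical analysis).
- RCT endpoint: 26 weeks after injection (Primary endpoints).
- One-year assessment: 52 weeks after the randomised injection or, in the extension, 52 weeks after the open-label injection (Study procedures).
- Earliest open-label injection: week 26 (Open label extension study; Randomization procedure and blinding).
- Last extension questionnaire before the one-year one: 26 weeks after the open-label injection (Study procedures).

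**Clock.** Let week 0 be the last woman's inclusion, L the delay from inclusion to the randomised injection, and M the delay from week 26 to the open-label injection. The case most favourable to the SAP is L = M = 0.

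**The RCT rule first.** L + 26 = 0 + 26 = 26 weeks. This reproduces the SAP's figure for the RCT.

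**The follow-up rule, counted from trial inclusion**

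| Data for the last woman | Formula | Earliest week | Stated week | Shortfall |
|---|---|---|---|---|
| One year after randomised injection | L + 52 | 52 | 26 | 26 |
| Extension, week 26 | L + 26 + M + 26 | 52 | 26 | 26 |
| Extension, one year | L + 26 + M + 52 | 78 | 26 | 52 |

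These are lower bounds. The SAP gives neither L nor M. With assumed delays of 0–4 weeks for L and 0–8 weeks for M, the earliest weeks become 52–56, 52–64 and 78–90.

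**The follow-up rule, counted from entry to the follow-up study.** If inclusion means entry at RCT week 26, the analysis falls at 26 + 26 = week 52. The shortfalls are then:

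- one-year follow-up: 52 − 52 = 0
- extension week 26: 52 − 52 = 0
- extension one year: 78 − 52 = 26 weeks

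**Share of women affected (illustration only).** The SAP gives no accrual period. Assume uniform accrual over A weeks, L = M = 0, extension participants spread evenly over accrual, and analysis exactly at the stated time. The share whose data are not yet due is the shortfall divided by A.

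| Trial-inclusion reading | A = 104 (2 years) | A = 156 (3 years) |
|---|---|---|
| No one-year data after randomised injection | 26/104 = 25% | 26/156 = 17% |
| Extension participants without one-year data after open-label injection | 52/104 = 50% | 52/156 = 33% |

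On the follow-up-entry reading, the first row becomes 0 and the second becomes 26/104 = 25% or 26/156 = 17%.

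**The case against.** The strongest defence is that inclusion, in a sentence about the follow-up study, means entry to that study. The RCT sentence refers to inclusion in the study; the follow-up sentence does not say what the woman is included in. The follow-up components start after the RCT, and entry to the extension is by separate offer. On this reading the analysis falls at about week 52, which fits both the one-year follow-up and the extension week-26 questionnaires. The reading is plausible, and the SAP does not rule it out. It does not rescue the extension's one-year questionnaires, which are still 26 weeks away, and the SAP does not define the term in this sense.

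A second defence is that cleaning of one-year outcomes cannot be finished before they have been collected, so the cleaning condition would delay the analysis in practice. This softens the defect. But the clause can be met by cleaning whatever has been collected, and nothing in the sentence requires one-year follow-up to be complete.

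A third is that the consequences are limited. This is fair: the primary and secondary 26-week analyses are untouched, and the sentence governs when a later report is written, not a test or an error rate.

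A reader might also infer that the RCT analysis is mistimed, because its clock starts at inclusion while the endpoint is counted from injection. The SAP does not support that. The RCT rule is a lower bound, it applies to outcomes defined from treatment, and it requires those outcomes to be cleaned, so it already allows for a gap before injection.

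**Conclusion.** The follow-up timing is wrong as written. Counted from trial inclusion, the last woman's one-year data come at least 26 weeks after the stated analysis, and an extension participant's one-year data at least 52 weeks after it. Under the more generous reading of inclusion the first gap closes and the second is still at least 26 weeks. Neither reading covers the extension's one-year questionnaires.

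Three limits apply.

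- A reader might infer that no follow-up data would exist at the analysis. That goes too far: women included early enough would already have completed their year, and the gap concerns later-included women.
- The 78 weeks is a minimum for an extension participant who was included last. It is not an upper limit.
- The percentages rest on an assumed uniform accrual over 2 to 3 years and are not properties of this trial. The week counts rest only on the SAP's schedule and on taking both injections at their earliest time.

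The sentence should be corrected before the follow-up analysis is run. It does not bear on the RCT result.

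**What to change.** Replace the follow-up sentence under Timing of final statistical analysis with two rules, each counted from injection:

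1. The one-year follow-up analysis is done no earlier than 52 weeks after the last randomised injection, once the one-year data have been cleaned.
2. The extension one-year analysis is done no earlier than 52 weeks after the last open-label injection, once those data have been cleaned. For that participant this is at least 26 + 52 = 78 weeks after her first injection. The extension week-26 data will by then be complete.

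If both are to appear in one report, the later date governs. Leave the RCT timing sentence as it is.

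The change is one of SAP wording only and asks for no new data. Its cost is a later follow-up report: at least 26 weeks later for the one-year follow-up on the trial-inclusion reading, and at least 26 or 52 weeks later for the extension, depending on how inclusion was meant.

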[**13.** **Tables** 11](#_Toc141888147)

[a. Baseline characteristics 11](#_Toc141888148)

[b. Primary outcome 12](#_Toc141888149)

[c. Safety outcomes 12](#_Toc141888150)

[d. Secondary outcomes 13](#_Toc141888151)

[**14.** **Figures** 14](#_Toc141888152)

[a. Flowchart of participants 14](#_Toc141888153)

[**15.** **References** 14](#_Toc141888154)

1. **List of abbreviations**

- BTA Botulinum toxin A
- CPP Chronic pelvic pain
- EQ-5D Quality of life questionnaire
- HADS Hospital Anxiety and Depression Scale
- MAPle Multiple Array Probe Leiden
- PCS Pain Catastrophizing Scale
- PFDI-20 Pelvic Floor Distress Inventory 20
- PFIQ-7 Pelvic Floor Impact Questionnaire 7
- PGI-I Patient Global Impression of Improvement
- PISQ-IR Pelvic Organ Prolapse/Incontinence Sexual Questionnaire, IUGA-Revised
- RCT Randomized controlled trial
- QoL Quality of Life
- VAS Visual Analogue Scale

1. **Introduction**
   1. Background

Chronic pelvic pain is common, affecting 15% of women aged 18-50^1^. Pelvic floor muscle spasms resulting in chronic pelvic pain may occur as a primary event or secondary to a physical, psychological or pathological factor. First-line treatment consists of pelvic floor physiotherapy. When first-line treatment fails, more invasive interventions can be done. One previously published intervention is injection with botulinum toxin A (BTA) in the pelvic floor muscles. It produces a localized, partial, and reversible chemical denervation of the muscle which results in localized muscle weakness or paralysis. There is some evidence that injection of BTA in the hypertonic pelvic floor muscles decreases pelvic pain in patients with therapy resistant chronic pelvic pain; however this is not investigated in a randomized controlled trial.

- 1. Objective

The primary objective of this randomized, double-blind, placebo controlled trial was to compare the effect of BTA injections vs. placebo injections on pelvic pain in women with chronic pelvic pain.

1. **Endpoints**
   1. Primary endpoints

Decrease of chronic pelvic pain, measured by a decrease in visual analog scale score (VAS score 0-10) with 33% and a patient global impression of improvement score (PGI-I) of 1 or 2 (better or much better) at 26 weeks after injection.

- 1. Secondary endpoints
     1. Subjective outcomes (patient reported outcomes)
- pelvic floor distress inventory (PFDI-20)^2^
- pelvic floor impact questionnaire (PFIQ-7)^2^
- quality of life (EQ-5D)^3^
- painDETECT^4^

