**Table 3. Primary outcomes.**

| Outcomes | BTA | Placebo | p-value |
| --- | --- | --- | --- |
| **Pain score** | N=xx | N=xx |  |
| Baseline | Mean (95% CI) | Mean (95% CI) |  |
| 4 weeks follow-up  8 weeks follow-up  12 weeks follow-up  26 weeks follow-up  BTA vs placebo*  Primary endpoint: 33% reduction in pain score, No. (%) | Mean (95% CI) Mean (95% CI) Mean (95% CI) Mean (95% CI)  NNN% | Mean (95% CI)  Mean (95% CI)  Mean (95% CI)  Mean (95% CI)  NNN% | X  X |
| **PGI-I** | N=xx | N=xx |  |
| 4 weeks follow-up  8 weeks follow-up  12 weeks follow-up  26 weeks follow-up  BTA vs placebo*  Primary endpoint: PGI-I 1 or 2, No. (%) | Mean (95% CI)  Mean (95% CI)  Mean (95% CI)  Mean (95% CI)  NNN% | Mean (95% CI)  Mean (95% CI)  Mean (95% CI)  Mean (95% CI)  NNN% | X  X |
| Data are presented as mean [95% CI] unless stated otherwise  *Pain score: average pain score last 4 weeks, scale 0-10.  **Based on linear mixed models including all time points except for baseline. Controlling for pain score (average past 4 weeks) at baseline and age at baseline.  *** p value for interaction | | | |

- 1. Secondary outcomes

| Outcome | Baseline n=xx | 26 weeks  n=xx | p-value |
| --- | --- | --- | --- |
| **PainDETECT total score** ^a^ |  |  |  |
| BTA  Placebo  *Botox vs. placebo | Mean (95% CI)  Mean (95% CI) | Mean (95% CI)  Mean (95% CI) | X |
| **Current VAS score^b^** |  |  |  |
| BTA  Placebo  *Botox vs. placebo | Mean (95% CI)  Mean (95% CI) | Mean (95% CI)  Mean (95% CI) |  |
| **EQ5D VAS score^c^** |  |  |  |
| BTA  Placebo  *Botox vs. placebo | Mean (95% CI)  Mean (95% CI) | Mean (95% CI)  Mean (95% CI) | X |
| **HADS depression scale^d^** |  |  |  |
| BTA  Placebo  *Botox vs. placebo | Mean (95% CI)  Mean (95% CI) | Mean (95% CI)  Mean (95% CI) | X |
| **HADS anxiety scale^d^** |  |  |  |
| BTA  Placebo  *Botox vs. placebo | Mean (95% CI)  Mean (95% CI) | Mean (95% CI)  Mean (95% CI) | X |
| **Pain catastrophizing scale (PCS)^e^** |  |  |  |
| BTA  Placebo  *Botox vs. placebo | Mean (95% CI)  Mean (95% CI) | Mean (95% CI)  Mean (95% CI) | X |
| **PFIQ-7 total score^f^** |  |  |  |
| BTA  Placebo  *Botox vs. placebo | Mean (95% CI)  Mean (95% CI) | Mean (95% CI)  Mean (95% CI) | X |
| **PFDI-20 total score^g^** |  |  |  |
| BTA  Placebo  *Botox vs. placebo | Mean (95% CI)  Mean (95% CI) | Mean (95% CI)  Mean (95% CI) | X |
| **PISQ-IR total score^h^** |  |  |  |

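### The SAP never analyses the primary endpoint it declares, states that endpoint in conflicting ways, and does not say which result decides the trial

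*SAP*

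**What the plan says.** - **Section 3, Primary endpoints.** The VAS decrease is specified as "with 33% and a patient global impression of improvement score (PGI-I) of 1 or 2 (better or much better) at 26 weeks after injection". Read plainly, both criteria must be met.
- **Section 4, Randomization procedure and blinding.** The same endpoint appears with the other conjunction: "Participants who did not meet the primary endpoint (33% reduction VAS score or PGI-I 1 or 2) were deblinded after 26 weeks".
- **Section 5, Sample-size.** N = 94 (47 per group) comes from an ANCOVA procedure for a 33% between-group difference in pain scores, at 80% power and two-sided alpha 0.05.
- **Section 7, Primary and secondary outcome analysis.** The hypothesis concerns pain only: "The null hypothesis entails that there is no significant difference in decrease of chronic pelvic pain scores 26 weeks after treatment". Two bullets labelled primary follow. For VAS: "Primary endpoint: Percentage difference in VAS score between baseline and 26 weeks post-treatment will be calculated for each group". For PGI-I: "Primary endpoint: the primary outcome of PGI-I scores being 1 or 2 (presented as median and interquartile (IQ) range) will be compared between groups".
- **Section 10, Comparison to study protocol.** The Kaplan-Meier estimate of 26-week success rates is dropped in favour of mixed models.
- **Section 11, Primary outcome.** Discrete outcomes are to be shown as numbers and percentages, with a relative risk or mean difference, 95% CI and p-value.
- **Section 13, Table 3.** One responder row begins "Primary endpoint: 33% reduction in pain score, No" and another, in a separate block, begins "Primary endpoint: PGI-I 1 or 2, No". No row joins them.

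**The concern.** An analyst who follows section 7 and fills in Table 3 will not produce the number of participants in each arm who met the endpoint of section 3. The analyst will instead have several results that can each be presented as primary, with nothing to say which one decides whether BTA worked. The rule could then be chosen after the results are known. The clash between *and* and *or* also affects trial conduct. A participant who meets exactly one criterion is a success under section 4 and a failure under section 3, and deblinding and the offer of the open-label extension depend on that classification.

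**Working it through.** **1. The definitions side by side**

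| Place in SAP | Quantity | Level | Comparison named |
|---|---|---|---|
| Section 3 | VAS criterion and PGI-I criterion | patient | none |
| Section 4 | VAS criterion or PGI-I criterion | patient | none (used for deblinding) |
| Section 5 | 33% difference in pain scores | continuous | ANCOVA-based N |
| Section 7, null hypothesis | decrease in pain scores | continuous | BTA against placebo |
| Section 7, VAS bullet | percentage VAS difference | group | none; only calculated |
| Section 7, PGI-I bullet | PGI-I 1 or 2 | patient, yes/no | compared; no test specific to this outcome |
| Table 3 | two separate responder rows | patient, yes/no | p-value column |

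The section 3 definition appears in none of the analysis or table entries.

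**2. Can the combined endpoint be recovered from Table 3?** No. If *a* of *n* participants in an arm meet the VAS criterion and *b* meet the PGI-I criterion, the number meeting both can lie anywhere from max(0, a + b − n) to min(a, b). The two margins do not determine it.

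**3. Median and IQR for PGI-I 1 or 2.** Coded 0/1, the median only shows whether more or fewer than half responded. Section 11 and Table 3 both call for counts and percentages.

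**4. Type I error for the two labelled endpoints, each tested at 0.05.** The SAP gives no correlation between the tests, so a range is assumed.

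- Either suffices, independent: 1 − 0.95² = 9.75%.
- Either suffices, correlated (simulated bivariate normal statistics, |z| > 1.96): 9.1% at correlation 0.5 and 7.8% at 0.8.
- Both required: at most 5%, because each must pass its own 5% test.

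**5. Power if both are required, each with 80%.** Independent: 0.80² = 64%. By simulation: 69% at correlation 0.5 and 73% at 0.8.

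**6. The stated sample size.** N = 94 can be neither confirmed nor refuted, because the SAP gives no SD, baseline mean, correlation or dropout rate. The ANCOVA formula is n per arm = 2(1 − ρ²)(1.960 + 0.842)²/d². With n = 47 it gives:

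- ρ = 0: d = √(2 × 7.849/47) = 0.578
- ρ = 0.5: d = 0.578 × √0.75 = 0.500
- ρ = 0.7: d = 0.578 × √0.51 = 0.413

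These are standardised differences in a continuous score, not differences in responder rates.

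**7. What 47 per arm gives a responder test.** Power = Φ{[δ√n − 1.96√(2p̄(1 − p̄))] / √(p₀(1 − p₀) + p₁(1 − p₁))}, where p₁ = p₀ + δ and p̄ is their mean. Placebo rates are assumed.

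| Placebo rate p₀ | Difference detectable at 80% power | Power for a 20-point difference |
|---|---|---|
| 10% | 23.6 points | 68% |
| 20% | 27.0 points | 56% |
| 30% | 28.4 points | 51% |
| 40% | 28.5 points | 49% |

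**The case against.** The best defence is that the objective, the null hypothesis and the sample size all concern pain scores, so one VAS comparison at two-sided 0.05 is implicitly the primary test. That is a fair reading of those three places. But the SAP never names that comparison as decisive. It attaches the primary label to other quantities, and it is not the endpoint declared in section 3.

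A second defence is that two co-primary endpoints were meant. The heading in section 3 is plural, section 7 gives each measure its own bullet, section 12 defines them separately, and Table 3 is titled in the plural. This also has force: the document does not establish that a single composite was intended. Co-primary endpoints would still need a stated both-must-succeed rule, and there is none.

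Two smaller points stand. The VAS responder classification is not absent, since Table 3 counts it by arm. And the median and IQR wording is probably a slip for the ordinal PGI-I score, which makes it easy to correct but leaves it contradictory as written.

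A reader might infer that the p-value cells in Table 3 give four chances of primary success, which for independent tests would be 1 − 0.95⁴ = 18.5%. The document does not support that count. Only two rows carry the primary label, and the table layout was flattened in text extraction, so the p-value cells cannot be matched to rows with certainty.

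**Conclusion.** The point holds. Sections 3, 4, 7 and Table 3 disagree on what the primary endpoint is, no analysis or table row delivers the endpoint declared in section 3, and no rule says which result decides the trial.

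The plan therefore leaves its type I error unfixed. It is 9.75%, or about 7.8% to 9.1%, if either labelled endpoint suffices, and at or below 5% with joint power of about 64% to 73% if both must succeed. These figures assume that each endpoint is tested at 0.05, that each has 80% power for the joint figure, and that the tests correlate between 0 and 0.8.

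It would be tempting to conclude that the trial cannot answer its primary question at 5% error. That goes too far. The SAP states no either-suffices rule, and both a both-must-succeed rule and a single pain-score test would keep the 5% level. The defect is that the choice is left open.

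**What to change.** Reconcile section 3, the blinding text in section 4, section 7 and Table 3 to one definition of the primary endpoint.

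- **For the composite as declared in section 3:** define one week-26 responder flag per participant. Test it once between arms at two-sided 0.05. Report n/N (%), relative risk and risk difference with 95% CI in a single Table 3 row labelled as primary. List the VAS and PGI-I components and the mixed models as supportive.
- **Missing data:** state how the flag is set when week-26 data are missing. Section 6 relies on mixed models and otherwise offers only loosely worded random imputation.
- **Alternative:** declare VAS and PGI-I as co-primary endpoints with an explicit rule that both must succeed, and state the joint power.
- **Deletions in section 7:** remove the median and IQR presentation for PGI-I 1 or 2, and remove the group-level percentage difference as a primary analysis.
- **Baseline adjustment:** this is optional. Section 7 removed it while the Table 3 footnote still mentions it, so reinstating it would have to be done openly.

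The cost is SAP wording and one table row, with no new data. Two consequences should be accepted openly. A significant result on one component alone no longer counts as primary success. And the stated 80% power refers to pain scores, so it should not be claimed for the responder test, where 47 per arm detects about 24 to 29 percentage points at 80% power for assumed placebo rates of 10% to 40%.
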